# Study design

The study is a **multicenter, exploratory, prospective open-label study**. Due to **the multimodal therapy concept**, a comparison of the different therapy approaches will be conducted.

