### Embolotherapy: Invasive therapy is indicated in patients with progressive symptoms according to the Schobinger classification. Historically, open surgical ligation and resection of the nidus had been considered the treatment of choice. However, embolization offers a less invasive way of treatment with lower morbidity and acceptable results. In some cases preoperative embolization is an option when complete surgical resection of the nidus is achievable thereafter.

The goal of endovascular embolotherapy is to occlude the nidus or fistulas completely. Commonly used agents are ethanol, N-butyl cyanoacrylate (NBCA) and ethylene-vinyl-alcohol-copolymer (EVOH). Additionally, coils or vascular plugs are needed in some cases, but those only occlude the feeding vessels and never reach the actual nidus, therefore the use is considered as adjuvant, mere coiling of AMVs is nowadays obsolete. Many authors use a combination of the following embolic agents for the endovascular treatment of complex fast-flow malformations.

- *Ethanol.* If injected in the right manner, ethanol is a very potent embolic agent for the occlusion of symptomatic fast-flow malformations. However, there is a high risk of tissue necrosis, nerve injury, and even cardiocirculatory arrest. Because of its low viscosity ethanol passes the nidus very quickly centrally into the lung circulation. Therefore, the pulmonary arterial pressure (PAP) should be monitored continuously during ethanol application. PAP above 25mmHg systolic can be found 10 to 15 minutes after application. To avoid side effects many interventionalists administer less than 0.5 ml per kg.
- *N-butyl cyanoacrylate (NBCA):* N-butyl cyanoacrylate (NBCA) and derivatives are liquid adhesive agents that polymerize irreversibly when exposed to blood. To adjust polymerization time and to enable fluoroscopic visibility NBCA is commonly mixed with lipiodol (ratio, 1:1 to 1:5). One major drawback of NBCA is the potential risk of catheter tip adhesion inside the lesion and the passive, flow-directed administration.

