## Secondary Endpoints

- Therapeutic efficiency and clinical outcome of the selected therapeutic concept for AV malformation treatment at 12, 24, 36 months after completion of invasive treatment:
- *Physician-reported* signs: general appearance (for example swelling, pulsation, ulceration, cardiovascular health issues, bleeding) and location-specific signs (for example extremity length discrepancy, physical impairment)
- Radiological assessment
  - Evaluation of the therapeutic response depending on imagine outcome:
    - MR-angiographically measured reduction of the size (volume) of the nidus of the AVM
    - Degree of AVM devascularization (modified from Cho et al 2006 and 2008)^21,22^ before treatment to both primary and secondary endpoints:
      - 100% devascularization
      - 76-99% devascularization
      - 50-75% devascularization
      - < 50% devascularization
- Concordance between clinical and imaging outcome
- Changes in patient photographs (only qualitative analysis with Likert scale)
- Identification of potential biomarkers (as of now: Angiopoetin-I, Angiopoetin-II, S-endoglin, TGF-beta, Integrin beta-3, Ephrin-B2, HGF, Angiostatin, Endostatin, Endothelin, bFGF, VEGF, IL-6, PDGF, S100A8/9, S100B, PROX1, NRP2, PIK3CA including circulating free DNA) for prediction of therapy response or/and disease progression in an exploratory manner. For this purpose, an additional blood sample of about 10 ml blood is obtained for the study. In case of a clinically required biopsy of the vascular malformation, obtained material may similarly be assessed for additional tissue biomarkers.
- Recurrence rates:
  - Clinical recurrence (reappearance or aggravation of symptoms or findings which were initially regressive)
  - Imaging recurrence (recurrent increase in size or reperfusion of the vascular malformation after initial regression, occurrence of newly perfused AVM not detected before)
  - Recurrence rates/Progression after initial partial versus after complete response
  - Recurrence rates depending on the kind of treatment, the type of embolic agent (in the case of sclerotherapy, embolization), and the initial clinical findings of vascular malformation (initial size or the initial severity of symptoms)
- Other local and systemic side effects at the follow-up visit

Therapeutic safety of the selected therapeutic concept for AV malformation treatment

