## Description of the procedures

Potential study participants are screened on an interdisciplinary basis according to the inclusion criteria through the participating centers. The screening includes laboratory analysis and pre-interventional imaging with US/CT/MRI to confirm the diagnosis and to identify possible treatment options, which are performed with the routine clinical workup. Furthermore, the exact size assessment of the initial extent of the vascular malformation (volumetric measurements, flow characteristics) is being performed based on the cross-sectional imaging data.

After detailed study information (orally and written) and informed consent, the patient is included in the study. The pre-therapeutic assessment is composed of the same subjective (SF-36v2/SF-10, VAS, Likert scale of severity of symptoms) and objective (general appearance and location-specific signs) surveys that are done during the follow-up appointments. Following interdisciplinary consensus, multimodal treatment is initiated

**Compression treatment** is considered as the baseline therapy for all vascular malformations. Patients are supplied with custom made compression garments (class II). Depending on severity of disease, permanent compression therapy may be applied or temporary compression may be considered sufficient.

**Embolization** is performed under general anesthesia following standard operating procedures. Access to the lesion will either be gained via a transarterial, transvenous or percutaneous route, or a combination of the latter. For transarterial or transvenous access is gained via a femoral or brachial access using a 5-8 French-sized catheter equipment. If additional percutaneous access is required lesion will be punctured under ultrasound guidance using a 20-21G needle. After contrast injection digital subtraction angiograms are acquired and subsequently embolization is performed under fluoroscopy guidance. Periprocedural anticoagulation is performed using unfractionated heparin in a weight-adapted manner. Periprocedural antibiosis is not applied routinely. Depending on the extent and morphology of the lesion multiple treatment sessions will be required in order to achieve complete/near-complete embolization. All agents used for embolization purposes are CE-marked.

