In case of **surgical resections** of AVM tissue, surgery is performed after complete/near-complete embolization. Surgical resection is similarly performed under general anesthesia. Neuromonitoring will be routinely used in case of proximity of the AVM to major nerve structures. Surgical resection is limited to mass-forming AVM tissue, complete resection of the entire malformation is rarely possible and not goal of the procedure.

Peripheral venous blood samples will be obtained on the day before, on day 1 and 3 following embolization as well during follow up at the same time points of health related QoL assessment. Blood samples will be processes and subsequently frozen until subsequent biomarker analysis.

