# Statistics

Analysis of clinical patient data, QoL data and Biomarkeranalysis will be performed separated from each other in a blinded setting. The study has an exploratory focus. All statistical testing will be performed based on a significance level of α=5%. No adjustment for multiple testing is planned.

Standard descriptive statistics will be used when reporting the study data. For continuous data, distribution parameters (mean, standard deviation, minimum, median, and maximum) will be computed and for categorical data, frequency counts will be given. If needed, 95% confidence intervals will be specified.

For the primary study parameters (scores PCS and MCS from adult SF-36v2 quality of life questionnaires, as well as PHS and PSS from kids SF-10 questionnaires), paired t-tests will be calculated comparing the scores at baseline to the respective scores at 6 months after the end of treatment (for embolized patients) or at the 24 months FU (for patients with conservative or medical treatment).

All QoL scores and subscores, as well as patient and physician reported pain and symptom data will be tabulated by study visit. Where appropriate, such data will also be summarized for different patient subgroups (e.g., age group, Schobinger stage, study treatment, etc.)

Morbidity, Mortality, and recurrence rates will be compared for different patient subgroups using Chi Square or Fisher’s exact test.

Summary statistics for AVM nidus volume reduction will be presented stratified by clinical outcome, as well as by patient subgroups, as needed. Crosstabulations of AVM devascularization (100% / 76-99% /50-75% / < 50% devascularization) vs. different clinical outcomes will be presented.

A sample size of N=74 (for children and adults, respectively) achieves 80% power to detect a mean of paired differences of 5 with an estimated standard deviation of differences of 15 and with a significance level (alpha) of 0,05 using a two-sided paired t-test.

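### Therapies are to be compared by crude chi-square or Fisher tests although treatment follows disease severity, so between-therapy differences can reflect baseline severity or lesion type

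*Protocol*

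**What the plan says.** The Study design section describes a "multicenter, exploratory, prospective open-label study" and adds that, because the concept is multimodal, "a comparison of the different therapy approaches will be conducted". Secondary Endpoints lists "Recurrence rates depending on the kind of treatment, the type of embolic agent", together with initial size and initial symptom severity as further factors.

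The Statistics section names the method: "Morbidity, Mortality, and recurrence rates will be compared for different patient subgroups using Chi Square or" Fisher's exact test. It does not say in that sentence which subgroups are meant. The preceding paragraph, on summaries of quality-of-life (QoL), pain and symptom data, gives as examples "age group, Schobinger stage, study treatment, etc". Testing is at 5% without multiplicity adjustment. No stratified test, regression, weighting or caution about interpretation is stated for any comparison by therapy.

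On how patients come to a treatment:
- The Embolotherapy part of the background says "Invasive therapy is indicated in patients with progressive symptoms according to the Schobinger classification".
- Description of the procedures says "Following interdisciplinary consensus, multimodal treatment is initiated", and makes the extent of compression depend on severity.
- The same section says that, where tissue is resected, "surgery is performed after complete/near-complete embolization".
- The background text on agents gives plugs and coils their role by angiographic lesion type (type I, and outflow occlusion in type II).

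**The concern.** When severity helps decide the therapy and also affects the outcome, a crude two-by-two test of therapy against outcome mixes the effect of severity with any effect of therapy. The protocol itself treats severity as possibly prognostic, since it plans to look at recurrence by initial size and symptoms. But it does so one factor at a time and never together with treatment.

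The comparison of therapies is one the design section promises, and the rationale presents the study as a source of missing evidence and of better patient selection. A significant crude difference in recurrence or morbidity between therapies, or between agents, could be taken as a difference in how well they work when it only shows who received them.

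**Working it through.** **The plan's own figure.** The sample size of 74 per age group is for a paired t-test (mean difference 5, SD 15, two-sided 5%, 80% power). With the exact noncentral t distribution, 73 is the smallest sufficient number and 74 gives 80.8% power, so the figure reproduces. It sizes the before-after test only; no comparison between therapies has been sized.

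**Inputs for the illustration.** The total of 148 patients is from the Study population section. Everything else is assumed, because the protocol gives no recurrence rates and no severity mix by therapy:
- recurrence 40% in severe and 15% in mild disease, the same under both therapies, so there is no treatment effect;
- group sizes 110 vs 38 or 74 vs 74 (the second is simply an even split; the protocol's 74 refers to age groups, not therapies);
- share of severe patients as in the table.

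**Formulas.** Crude rate = share × 0.40 + (1 − share) × 0.15. The spurious difference is therefore (share A − share B) × 0.25. The rejection probability is the sum of the binomial probabilities of all outcomes for which the test gives p < 0.05.

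| Severe, A vs B | Crude rates | Spurious difference | Chi-square rejects, 110/38 | Chi-square rejects, 74/74 | Fisher rejects, 110/38 and 74/74 |
|---|---|---|---|---|---|
| 50% vs 50% | 27.5% vs 27.5% | 0 | 4.8% | 5.1% | 3.9%, 3.2% |
| 55% vs 45% | 28.75% vs 26.25% | 2.5 points | 5.4% | 6.4% | 4.5%, 4.2% |
| 60% vs 40% | 30% vs 25% | 5 points | 8.0% | 10.6% | 7.0%, 7.4% |
| 70% vs 30% | 32.5% vs 22.5% | 10 points | 19.7% | 27.8% | 18.1%, 21.8% |
| 70% vs 20% | 32.5% vs 20% | 12.5 points | 29.5% | 41.2% | 27.4%, 34.0% |

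Hand check of one cell (74 vs 74, 70% vs 30%): the standard error is √(2 × 0.275 × 0.725 / 74) = 0.0734, the expected z is 0.10 / 0.0734 = 1.36, and P(Z > 1.96 − 1.36) is about 27–28%.

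**Fewer patients at risk.** Recurrence is defined mainly as return after initial regression. If 60% regress in each group (assumed), 110 vs 38 becomes 66 vs 23, and chi-square rejection at 70% vs 20–30% severe falls to 13–19%. If few conservatively treated patients regress (66 vs 10), it is 7–9% (Fisher 4–5%). The spurious difference in rates stays the same; only the chance that it reaches significance falls.

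**What stratifying does.** Within each severity level the two therapies have the same rate by construction, so a stratified comparison has nothing spurious to detect. In a separate simulation (4,000 runs per scenario, mild/severe rates of 10/30%, 15/45% and 20/50%, up to 80% vs 20% severe), a severity-stratified Mantel-Haenszel test rejected in 4–6% of runs throughout. The crude chi-square test reached 45–68% at 74 vs 74 in the most unbalanced setting.

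**The case against.** Several points on the other side carry weight.

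- **Scope of the test sentence.** It says only patient subgroups. Study treatment is named in a different paragraph, and embolic agent is not named in the Statistics section at all. That the crude test covers therapy and agent is therefore a reading, though a natural one: the design promises a comparison of therapies, recurrence by treatment and agent is an endpoint, and no other between-group test is given.
- **Left to the analysis plan.** Adjustment models often are, and the protocol does not exclude them. But here the protocol itself names the unadjusted test, and an analysis plan that follows it inherits the problem.
- **Exploratory label.** It lowers the weight of any p-value. It does not remove confounding.
- **Size.** With a mild imbalance the false-positive rate is close to nominal. The large figures need imbalances of 40–50 points.

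Three stronger readings are tempting, and the protocol does not support them. A reader might infer that severity differences will be reported as treatment effects; the protocol makes no such causal claim, and recurrence by initial severity is to be shown as well. A reader might extend the Schobinger argument to the choice of agent; that sentence concerns when invasive therapy is indicated, and the text on agents points to lesion type instead. A reader might think QoL is compared between therapies without adjustment; QoL is only summarised by subgroup, and its test is within-patient.

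**Conclusion.** The point holds for morbidity, mortality and recurrence compared by therapy, and by lesion type rather than stage for recurrence by embolic agent. The method as stated yields contrasts that can reflect baseline differences, and nothing in the protocol separates these from treatment.

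The size cannot be fixed from the document. Under the assumed rates, the crude comparison is off by a quarter of the imbalance in severity: 2.5 points at 55% vs 45% severe, and 10–12.5 points at 70% vs 20–30%. The false-positive rate of the chi-square test ranges from near nominal (5–6%) through 8–11% to 20–41%, and is lower when only patients with initial regression count. The existence of the bias follows from how treatment is chosen, provided severity or lesion type affects the outcome; its direction and magnitude are unknown.

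This should be corrected, but it does not touch the primary endpoint, whose paired test compares patients with themselves.

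**What to change.** In the Statistics section:

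1. For recurrence and morbidity by therapy, replace the crude test with an estimate stratified by or adjusted for Schobinger stage and at most one or two further baseline factors, for example initial nidus size and age group. Report it with a 95% confidence interval. A larger model is not realistic with 148 patients spread over several overlapping therapy groups.
2. For recurrence by embolic agent, stratify or adjust by angiographic lesion type.
3. Where events are too few (mortality, small groups), or where groups are formed after baseline (surgery after embolization), report rates descriptively without p-values. Baseline adjustment does not repair a grouping that depends on how earlier treatment went.
4. State that comparisons between therapies are non-randomised and not to be read causally.

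The cost is a change of wording and modest analysis work. Initial size, flow characteristics and symptom severity are already assessed before therapy, Schobinger stage is already a planned subgroup, and angiograms are acquired at embolization, although lesion type must be recorded in a usable form. The price is wider intervals and some comparisons that become purely descriptive.

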# Study population

A total of 148 patients with AV malformations will be treated across centers, of which approximately 50 patients will be treated at LMU University Hospital Munich.

## Inclusion Criteria

- Age: > 4 years, < 70 years
- Patients with simple peripheral (=extracranial) arteriovenous malformations according to the ISSVA (International Society for the Study of Vascular Anomalies) classification. Each patient and the corresponding diagnosis, is discussed in an interdisciplinary board for vascular anomalies before initiation of treatment.
- Patients with combined vascular malformations and arteriovenous malformations associated with other anomalies (e. g. Parkes Weber, PTEN hamartoma, HHT) according to the ISSVA (International Society for the Study of Vascular Anomalies) classification
- Patients with first line therapy or patients with previous alternative therapies in whom the previous treatments did not lead to durable symptom improvement
  - Previous surgery or embolization are not an exclusion criterion, but these patients will only be included in case of a therapy-free interval of 12 months
- Adults and children will be similarly included

## Exclusion Criteria:

- Patients with AV malformations located in the central nervous system
- Patients with AV malformations located in abdominal parenchymal organs or the gastrointestinal tract
- Patients with other high-flow vascular anomalies (e. g. vascular tumors)
- Patients who have been previously treated by surgery or sclerotherapy/embolization within the last 12 months
- Patients with concomitant life-limiting diseases (such as cancer)
- Patients with acute inflammatory diseases or acute bacterial superinfection of an AVM related ulceration
- Patients with contraindications for invasive treatments
  - Patients with contrast agent intolerance or renal insufficiency (GFR>30ml/min)
  - Patients with impaired coagulation status:
    - Platelet count <50.000 / μl
    - aPTT > 50s
    - INR > 1,5
  - Poor general condition with ECOC performance > 1
- Pregnant or breast-feeding women
- Inability to access the AVM lesion due to anatomical or pathoanatomical reason
- Inability of the patient/parents to understand or follow the study protocol e.g. due to impaired mental health status
- Patients/parents who refuse to give informed consent

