# Adverse events (AE) / serious adverse events (SAE)

Adverse events are considered to be directly or indirectly related to the study protocol. A serious adverse event is considered to be a study-related AE that:

· leads to death.

· is life-threatening (the danger to life must have actually existed; it is not enough that the event could have led to death if it would have been more serious).

· requires hospitalization or prolongs a hospital stay.

· leads to a permanent and significant disability.

The invasive therapy regimens as listed above can cause a variety of side effects and procedure related complications. As those events are however not related to the observational character of the study protocol, those are not considered to be Adverse Events (AE) or Serious Adverse Events (SAE).

Procedure-related events, not considered to be AE/SAE:

· Bleeding up to hypovolemic shock with indication for blood transfusion or emergency intervention/surgery

· Infections with consecutive systemic spread up to sepsis/shock including septic arthritis

· Damage caused by ionizing radiation (especially radiation dermatitis)

· Unforeseen Injury to tissue adjacent to the AVM, especially soft tissue, skin, vessels and nerves

· Unforeseen cardiovascular disorders such as pulmonary embolism and stroke

· Contrast medium or drug-induced renal failure, which may require dialysis treatment

· Contrast medium-induced thyroid disorders

· Allergic reactions

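### The renal exclusion names renal insufficiency, but its inequality (GFR above 30 ml/min) excludes patients with better kidney function and lets through those at or below 30.

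*Protocol*

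**What the plan says.** In the Protocol, Study population, Exclusion Criteria, the renal item reads "Patients with contrast agent intolerance or renal insufficiency (GFR>30ml/min". It is a sub-item of "Patients with contraindications for invasive treatments". The same list gives numerical limits for coagulation, for example "Platelet count <50.000 / μl", together with aPTT above 50 s and INR above 1.5, and it excludes a performance status above 1.

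Two other sections show why the renal item is there. Description of the procedures says of embolization: "After contrast injection digital subtraction angiograms are acquired and subsequently embolization is performed under fluoroscopy guidance". It adds that several sessions may be needed, depending on the lesion. The section on adverse events lists "Contrast medium or drug-induced renal failure, which may require dialysis treatment" among the procedure-related events that are not counted as AE or SAE.

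No other section of the Protocol restates the renal criterion or gives another GFR limit.

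**The concern.** The label and the operator point in opposite directions. A low GFR means poor kidney function, so a criterion meant to exclude renal insufficiency cannot be defined by a GFR above its threshold. The bracket is the only part that a study nurse, a monitor or an electronic check can apply without judgement.

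Two things are at stake. The first is who enters: a site that works from the number and a site that works from the words enrol opposite groups under the same criterion. The second is protection. The Protocol itself names contrast-induced renal failure, possibly needing dialysis, as a risk of the procedure, and this item is its only specific renal safeguard at entry. Read by its number, the item lets through the patients whom its words set out to keep out.

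**Working it through.** The criterion states no derived figure, so there is nothing to reproduce. The check is logical.

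**Step 1. Apply the rule as written.** The rule is: exclude if GFR > 30 ml/min. The third column turns the sign round, only to show how far the outcome depends on it. It is not a proposed limit.

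| GFR (ml/min) | As written (exclude if > 30) | Sign turned round (exclude if < 30) |
|---|---|---|
| 15 | not excluded | excluded |
| 29 | not excluded | excluded |
| 30 | not excluded | not excluded |
| 31 | excluded | not excluded |
| 45 | excluded | not excluded |
| 60 | excluded | not excluded |
| 90 | excluded | not excluded |
| 120 | excluded | not excluded |

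The decision flips at every value except exactly 30, which neither strict inequality excludes. As written, the lowest GFR values pass and the highest fail.

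**Step 2. Compare with the sibling thresholds.** Each item in this part of the list has a label or heading that names an impaired state, and a sign.

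| Item | Sign and limit | Side excluded | Agrees with its label? |
|---|---|---|---|
| Platelets | < 50,000 per μl | impaired | yes |
| aPTT | > 50 s | impaired | yes |
| INR | > 1.5 | impaired | yes |
| Performance status | > 1 | impaired | yes |
| GFR | > 30 ml/min | better function | no |

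Only the renal item points away from its own label. The neighbouring signs, in both directions, read sensibly, so a fault in reading the text is not a plausible explanation.

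**Step 3. Look for a correction elsewhere.** Description of the procedures refers to screening laboratory analysis in general terms. The flowchart legend's routine laboratory panel lists blood count, coagulation, electrolytes, CRP and TSH. Neither states a renal limit. The flowcharts themselves are not available, so this does not show that renal function goes unmeasured. It shows only that the available text has no second statement to settle the conflict.

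**Step 4. Consequence under each reading.**
- *By the number:* patients above 30 ml/min fail screening and those at or below 30 pass.
- *By the words:* patients with adequate kidney function are enrolled, yet each one above 30 ml/min meets a written exclusion criterion.

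Under Study population, 148 patients are planned, about 50 of them at the lead hospital. About 148 − 50 = 98 would then be screened at other centres, which depend on the written rule.

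**The case against.** The strongest reply is that the bracket qualifies a noun and is not a free-standing rule. A patient with normal kidneys does not have renal insufficiency, so the sentence taken as a whole does not exclude that patient. The parent heading on contraindications and the correctly signed neighbours make the intent easy to infer. Each patient is discussed by an interdisciplinary board before treatment. The flowchart legend says that the treatment procedure is not part of the observational study, so entry does not by itself assign contrast. A study that really excluded GFR above 30 could hardly recruit, and the mistake would show at once. The error does not touch the primary endpoint, the analysis or the sample size.

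Much of this stands. An experienced clinician would very probably follow the words, and no evidence shows that any centre has done otherwise. The loss of the whole target population is a consequence of the literal reading, not a forecast. The adverse-event section supplies context on the risk and is not a second instance of the contradiction. The screening form and the recruitment status are not shown, so any error there is only a possibility.

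None of this makes the criterion correct. If the intent has to be inferred against the written number, the number is wrong or the label is. Relying on that inference also leaves enrolled patients in formal breach of the text.

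**Conclusion.** The concern holds. The renal exclusion contradicts itself, and as written its threshold excludes GFR above 30 ml/min and admits 30 or below. On the literal reading that removes essentially all of the intended children and adults and retains the group that the label names. The Protocol gives no GFR distribution, so no exact percentage can be stated; the size rests on the assumption that most candidates have kidney function above 30 ml/min. On the reading by words, nearly every enrolled patient becomes a formal eligibility deviation. The label, the parent heading and the siblings all suggest that the sign is at fault. Which cut-off is clinically right is not judged here. Because this is an operative eligibility threshold tied to a named procedural harm, it must be corrected.

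**What to change.** Reconcile the inequality with the words, so that the criterion excludes the patients it names. In the same edit the clinical lead should confirm the cut-off and its unit, and state how a value of exactly 30 is handled, since a strict inequality leaves it out in either direction.

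Then check whether the CRF or any screening form copied the sign, and correct it if so. If patients have already been screened, review their renal entries against the corrected criterion and document any deviation.

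The cost is small: one character if only the sign is wrong, slightly more if the cut-off or unit also changes, plus a check of the form. The sample size and the analysis are unaffected.
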